**Methods/design:**

We will conduct a randomized clinical trial with three groups: a real multimodal group (RMG), a virtual multimodal group (VMG), and a combined multimodal group (CMG). It was estimated that we will need a sample of 36 participants (12 per group). RMG individuals will only perform multimodal physical exercises in a real environment two times per week for 60 min per session for 15 weeks. VMG individuals will perform exercises of the same duration over the same time frame but only in a virtual environment. CMG individuals will hold a weekly session in a real environment and another weekly session in virtual environment. The primary outcome measure will be health-related quality of life, evaluated using the Stroke Impact Scale; effects on cognition (Montreal Cognitive Assessment), balance (Berg Balance Scale), mobility (Timed Up & Go), self-selected gait speed (10-meter walk test), and gait functional capacity (6-min walk test) will be investigated as secondary outcome measures. Participants will be evaluated before the beginning of the intervention, immediately after the end of the intervention, and at 1-month follow-up without exercise. If the data meet the assumptions of the parametric analysis, the results will be evaluated by analysis of variance (3 × 3) for the group factor, with repeated measures while taking into account the time factor. The post hoc Tukey test will be used to detect differences (α = 0.05).

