Saposnik and Levin [18] claimed there were few publications regarding the combination of multimodal physical exercises in real and virtual environments. Most of the existing studies did not investigate long-term effects, including follow-up, and added intervention time to the experimental groups, which provided them with an advantage in the total intervention time received. In addition, there is an important diversity in the literature regarding the profile characteristics of individuals with stroke, considering acute, subacute, and chronic patients. Thus, the results found in the previous studies [19–24] do not allow consistent conclusions to be made about the effects of the combination of multimodal exercises in real and virtual environments in individuals after chronic stroke.

This study seeks to answer whether the combination of multimodal physical exercises in real and virtual environments could bring additional benefits to the quality of life, cognition, gait, and balance of individuals after chronic stroke. We also intend to clarify the effects of interventions with multimodal physical exercises when performed only in a real environment or only in a virtual environment and to investigate whether the possible effects remain after 1 month without participating in physical exercises.

This study aims to investigate the effects of a protocol of multimodal physical exercises in real and virtual environments for individuals who have survived a stroke.

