### Outcome measures and outcome assessment

The primary outcome will be the domain “activities of daily living” from the Stroke Impact Scale (SIS). This will be used to measure the individuals’ levels of participation. As secondary outcome measures, the other domains from the SIS will be used, as well as their total score and the percentage of recovery from stroke, for the purpose of measuring the range of structures/functions and activities. These will be measured using the Montreal Cognitive Assessment (MoCA), Berg Balance Scale (BBS), 6-minute walk test (6MWT), 10-meter walk test (10MWT), and Timed Up & Go Test (TUG).

All measurements will be carried out by trained evaluators who will not be involved in the interventions and will be blinded to the allocation of individuals to the groups. All individuals will be evaluated at three moments: before the beginning of the interventions (baseline), immediately after the end of the interventions (posttest), and 1 month after the end of the interventions (follow-up). The schedule of enrollment, allocation, and postallocation is provided in Table 1.

**Table 1 Tab1:** Outcomes assessment time-points and instruments

	Instruments/methods	Enrolment	Baseline	Allocation	Post allocation	
					Post test 15 weeks	Follow up 19 weeks
Eligibility screen: Socio-demographic variables	Structured interview, recording age, brain injury, schooling and medical history	X				
Informed consent	Informed Consent Term	X				
Allocation	3 intervention groups: RMG, VMG or CMG			X		
Quality of life	SIS		X		X	X
Cognitive	MOCA		X		X	X
Gait Functional Capacity	6MWT		X		X	X
Self-selected gait speed	10 MWT		X		X	X
Mobility	TUG		X		X	X
Balance	Berg Balance Scale (BBS)		X		X	X

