### Measurements

*Quality of life* will be evaluated through the SIS. This scale evaluates quality of life by measuring 59 items categorized in 8 domains: strength (4 items), hand function (5 items), activities of daily living/instrumental activity of daily living (10 items), mobility (9 items), communication items [7], emotion (9 items), memory and reasoning (7 items), and participation function (8 items). Each item is rated on a 5-point Likert scale in terms of difficulty the patient has experienced in completing each item. Summative scores will be generated for each domain, ranging from 0 to 100. An extra question will be asked in order to know, on a scale from 0 to 100, how much the individual feels they have recovered since their stroke. Our primary outcome measure will be the domain of the activities of daily living/instrumental activity of daily living, and the rest of the domains will be used as secondary outcome measures [34]. The Brazilian version of SIS 3.0 has satisfactory internal consistency, test-retest reliability, convergent validity, and discriminant validity in stroke patients [34]. SIS 3.0 is a specific measure of psychometrically robust HRQoL that can be useful in assessing the consequences of stroke in different cultural contexts [34]. For some of the domains that make up this scale, there are values of minimum detectable change (MDC) and clinically important difference (CID). According to Lin et al. [35], the values are strength (MDC 24.0 and CID 9.2), activities of daily living/instrumental activities of daily living (MDC 17.3 and CID 5.9), mobility (MDC 15.1 and CID 4.5), and hand function (MDC 25.9 and CID17.8).

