### Statistical analysis

It was estimated that a sample of 36 participants (12 per group) would provide 88% power (α = 5%) to detect a difference between group means of 17.3 (MDC of the activities of daily living/instrumental activities of daily living domain of the SIS) using the program G*Power 3 [48], which takes into account the number of sample groups and the number of evaluation measures. To reach this total number of individuals, at least 43 individuals must be recruited, allowing a dropout rate of 20%.

For the mathematical treatment and statistical analysis of the data, Excel software (Microsoft, Redmond, WA, USA) will be used for the tabulation of data, and SPSS version 13 software (SPSS, Chicago, IL, USA) will be used for statistical analyses. A significance level of 5% will be adopted. Initially, for the characterization of the sample, descriptive analysis and the *t* test will be used to examine differences between the RMG, VMG, and CMG groups. Subsequently, for the analysis of the normality and homogeneity of the results of the primary outcome measure and secondary outcomes, the Shapiro-Wilk and Levene tests will be used, respectively. After observing the assumptions for normality and homogeneity, parametric analysis will be performed using two-way analysis of variance (3 groups by 3 moments [baseline, post-test, and follow-up]) and post hoc Tukey test. The mean between-group difference and 95% confidence intervals will be reported for all outcomes. If any subject gives up the protocol, their measured outcomes will be analyzed on an intention-to-treat basis.

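### The 3x3 ANOVA treats the pre-allocation baseline as an outcome level and plans no baseline adjustment; a baseline-adjusted comparison of the later scores is never materially worse and, if Tukey is applied to the group factor, far better

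*Protocol article*

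**What the plan says.** The Statistical analysis section fixes the method for the primary and secondary outcomes: once normality and homogeneity have been checked, "two-way analysis of variance (3 groups by 3 moments [baseline, post-test, and follow-up]) and post hoc Tukey test". The abstract describes the same analysis as a 3 × 3 ANOVA "for the group factor, with repeated measures while taking into account the time factor", followed by Tukey.

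The primary outcome is defined under Measurements: "Our primary outcome measure will be the domain of the activities of daily living/instrumental activity of daily living". Table 1 places the baseline assessment before allocation, with post-test at 15 weeks and follow-up at 19 weeks.

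For reporting, the Statistical analysis section says: "The mean between-group difference and 95% confidence intervals will be reported for all outcomes". It names no time point for that difference and no adjustment for baseline. The Background states the question as "whether the combination of multimodal physical exercises in real and virtual environments could bring additional benefits". It also asks about each single environment and about persistence one month later.

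**The concern.** Randomisation makes the expected baseline difference between groups zero. Entering baseline as one of three equally weighted outcome levels can therefore only pull a group mean difference towards zero. Baseline is most useful as a covariate, where it removes between-patient variation from the later scores, and the plan does not use it that way.

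The article also leaves open which ANOVA term carries the conclusion and what Tukey is applied to. The group main effect averages over all three moments. The group-by-moment interaction compares changes over time, but it is a 4-df omnibus test, and by itself it does not say whether the combined group did better than either single environment.

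With 12 patients per group, precision is scarce and chance baseline imbalance is likely. A fraction r of that imbalance passes into an unadjusted later difference, where r is the between-visit correlation. A fraction 1 − r passes into a change score in the opposite direction. Covariate adjustment removes both.

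**Working it through.** **Inputs from the article.** Three groups of 12, three moments, and a 5% level. The design difference is 17.3 points (the minimum detectable change of the ADL/IADL domain) and the stated power is 88%.

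**Assumed, because the article does not give them.** SD 15 or 20 at each visit; correlation r between any two visits of 0.5, 0.7 or 0.8 (compound symmetry).

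**The plan's own figure.** The 88% cannot be reproduced without an SD, a correlation and the G*Power term used. It is attainable in several ways: a two-group comparison with SD about 13.5, a between-group effect f = 0.49 at r 0.5, or an interaction effect f = 0.27 at r 0.5. It therefore does not show which term is meant to be decisive.

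**Step 1: expected size of the contrast when the true difference at 15 weeks is 17.3.**
- Group mean over three moments, effect sustained: (0 + 17.3 + 17.3)/3 = 11.5.
- Group mean over three moments, effect lost by follow-up: (0 + 17.3 + 0)/3 = 5.8.
- Change from baseline to post-test (the interaction contrast): 17.3 − 0 = 17.3.
- Baseline-adjusted difference at post-test: 17.3.

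**Step 2: variance of a pairwise difference, relative to the unadjusted post-test difference** (variance 2·SD²/12, so the standard error is 6.12 at SD 15).
- Three-moment mean: (1 + 2r)/3.
- Change from baseline: 2(1 − r).
- Baseline-adjusted: 1 − r².

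At SD 15 and r 0.7 the standard errors are 6.12·√0.80 = 5.48, 6.12·√0.60 = 4.74 and 6.12·√0.51 = 4.37. Simulation with 20,000 runs gave 5.45, 4.74 and 4.42.

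**Step 3: baseline adjustment against change from baseline.** The variance ratio is (1 − r²)/[2(1 − r)] = (1 + r)/2. At r 0.5 it is 0.75, and √0.75 = 0.866, so the interval is about 13% narrower. At r 0.7 it is 0.85, and √0.85 = 0.922, about 8% narrower. At r 0.8 it is 0.90, and √0.90 = 0.949, about 5% narrower.

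**Step 4: Tukey-adjusted pairwise power for a true 17.3** (simulated; r = 0.5 / 0.7 / 0.8).

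| Comparison | SD 15 | SD 20 |
|---|---|---|
| Group means, effect sustained | 45 / 38 / 34% | 25 / 21 / 19% |
| Group means, effect lost by follow-up | 11 / 9 / 9% | 7 / 6 / 6% |
| Change to 15 weeks | 64 / 87 / 98% | 38 / 62 / 81% |
| Baseline-adjusted at 15 weeks | 77 / 92 / 98% | 49 / 68 / 84% |

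**Step 5: omnibus F tests, third group midway between the other two.** The interaction test has 4 and 66 df, with noncentrality 12·Σg²·(2/3)/[SD²(1 − r)]. The baseline-adjusted test has 2 and 32 df, with noncentrality 12·Σg²/[SD²(1 − r²)]. Here g is −8.65, 0, 8.65.

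| Test | SD 15 | SD 20 |
|---|---|---|
| Group-by-moment interaction | 71 / 92 / 99% | 44 / 68 / 86% |
| Baseline-adjusted | 80 / 93 / 99% | 54 / 72 / 86% |

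The gain is 9 to 10 points at r 0.5 (8 at SD 25), 1 to 4 at r 0.7 (5 at SD 25), and none at r 0.8 (1 at SD 25).

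**The case against.** The strongest defence is that a 3 × 3 repeated-measures ANOVA in a randomised trial is conventional and valid through its group-by-moment interaction. That test compares changes over time, does not dilute the effect and does use baseline. This stands. Dilution to 11.5 or 5.8 follows only if group means are compared, and the abstract's mention of the group factor may merely describe the layout, with group between patients and time within. A reader might infer that the plan certainly runs Tukey on group, and so that it certainly falls from 92% power to 38%. The Statistical analysis section does not say what Tukey is applied to, so that contrast is conditional on one reading.

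A reader might also infer an ordinary two-way ANOVA that treats three scores per patient as independent, with type I error for group of some 23 to 31%, because the Statistical analysis section omits the repeated-measures wording. The documents do not support this. The abstract says "with repeated measures while taking into account the time factor. The post hoc Tukey test will be used to detect differences", and the sample-size calculation accounts for the number of evaluations. The two descriptions need only be brought into line.

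Nor does the article make 15 weeks the primary time point or rank the virtual-versus-real comparison as secondary. The Background asks about both single environments and about persistence, so those choices belong to the sponsor.

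Finally, covariate and covariance details are often left to an analysis plan that is not shown here. That excuses missing detail. It does not cover the stated choice to make baseline an outcome level.

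**Conclusion.** The point holds as an improvement whose size depends on the reading. The article fixes an analysis with pre-allocation baseline as an outcome level and plans no baseline adjustment of the between-group differences.

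If group means are compared, the loss is severe: one third to two thirds of the true effect remains, and pairwise power is less than two thirds of what baseline adjustment gives in every scenario examined. If the repeated-measures interaction is used, the analysis is sound, and baseline adjustment adds a modest gain that fades as the correlation rises.

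Under the assumed equal variances and correlations, the variance ratio (1 + r)/2 never exceeds 1, so the adjusted estimate is at least as precise as change from baseline, apart from the small cost of estimating one slope. The dilution figures follow from the design alone. All power figures rest on the assumed SD and correlation, which the article does not report.

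**What to change.** - Replace the 3 × 3 ANOVA as primary analysis with a repeated-measures model of the post-test and follow-up ADL/IADL scores. Use baseline ADL/IADL as covariate, with group, visit and group-by-visit. ANCOVA at a single visit is an acceptable alternative.
- Have the sponsor name the primary time point. Compare the three groups pairwise there, with Tukey adjustment at the 5% level already adopted.
- Report baseline-adjusted mean differences with 95% confidence intervals.
- State in the Statistical analysis section that the analysis is a repeated-measures one, so that it agrees with the abstract.

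The cost is a revised paragraph and light programming. All the data are already scheduled in Table 1, and no further patients are needed.

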### Study setting

A prospective, randomized trial with concealed allocation, blinded assessors, and intention-to-treat analysis will be carried out. The study will be conducted in the Motor Behavior Laboratory in the School of Physical Education and Sports at the University of Sao Paulo, Brazil.

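### Intention-to-treat is promised, but the only named analysis, a three-moment repeated-measures ANOVA, drops every participant with a missing assessment

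*Protocol article*

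**What the plan says.** Two places in the protocol article commit to intention-to-treat. Under Study setting: "A prospective, randomized trial with concealed allocation, blinded assessors, and intention-to-treat analysis will be carried out". Under Statistical analysis, for people who leave: "If any subject gives up the protocol, their measured outcomes will be analyzed on an intention-to-treat basis".

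The same Statistical analysis section names one analysis for the outcomes: "two-way analysis of variance (3 groups by 3 moments [baseline, post-test, and follow-up]) and post hoc Tukey test". The Abstract makes clear that time is a within-person factor: "analysis of variance (3 × 3) for the group factor, with repeated measures while taking into account the time factor". On software, "SPSS version 13 software (SPSS, Chicago, IL, USA) will be used for statistical analyses".

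Under Outcome measures and outcome assessment, "All individuals will be evaluated at three moments": baseline, posttest at 15 weeks and follow-up at 19 weeks. The sample-size paragraph wants 36 participants and recruits at least 43, allowing for 20% dropout. The article describes no step for using a participant whose set of three assessments is incomplete.

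**The concern.** A classical repeated-measures ANOVA works on complete sets of measurements. A participant who attends baseline and posttest but misses follow-up is removed entirely, so a posttest score that was measured is not analysed. A participant who leaves before posttest also drops out of the analysis. For these people the named method does the opposite of what the intention-to-treat sentence promises.

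The conflict affects the primary outcome (the activities of daily living domain of the Stroke Impact Scale) and every secondary outcome analysed the same way. The analysed set would then be the participants who completed all assessments, while the report could call it intention-to-treat. If loss depends on how people are doing and differs between the real, virtual and combined arms, the between-arm comparison is biased.

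**Working it through.** **1. What the text requires of each kind of participant**

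| Participant | Promise | Three-moment repeated-measures ANOVA |
|---|---|---|
| Stops sessions, attends all three assessments | Analysed as assigned | Included |
| Attends baseline and posttest, misses follow-up | Measured scores analysed | Deleted, including the measured posttest |
| Attends baseline only | Measured score analysed | Deleted |

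Promise and method agree in the first row and conflict in the other two.

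The Statistical analysis section alone says only two-way. An ordinary two-way ANOVA without the repeated-measures structure would keep the incomplete rows, but it would treat up to three scores per person as independent. That is no remedy, and the Abstract rules it out.

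**2. Number affected**

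Inputs from the Statistical analysis section: 36 needed, 43 recruited, 20% dropout.

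- The plan's figure reproduces as 36 × 1.2 = 43.2, stated as 43.
- Reading A, the plan's own target: 43 − 36 = 7 lost (7/43 = 16%).
- Reading B, 20% of those recruited: 43 × 0.8 = 34.4, so about 34 analysed and 9 lost (9/43 = 21%).

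Both readings assume that a dropout is someone with a missing assessment. If losses are independent with probability 0.20, the chance of fewer than 36 complete sets among 43 is P(X ≤ 35), X ~ Binomial(43, 0.8), which is about 65%.

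**3. Power**

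The stated 88% cannot be rebuilt directly, because the article gives neither an SD nor a within-person correlation. It can be back-solved from the noncentral F distribution for repeated-measures ANOVA with 3 groups, 3 measures, N = 36 and an assumed correlation of 0.5. The effect size giving 88% is f = 0.49 for the between-group test or f = 0.27 for the group-by-time interaction. Holding f fixed:

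- N = 34: about 86% for either test.
- N = 43: about 94% for either test, if all contributed fully.

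The loss against the plan's 88% is about 2 percentage points.

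**4. Bias, as an illustration only**

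Assumed, not in the documents: score SD 15; correlation 0.7 between baseline and posttest; loss after posttest and in one arm only; log-odds of loss rising by 1 for each SD of poorer change.

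- SD of change = 15 × √(2 × (1 − 0.7)) = 11.6.
- Bias = 11.6 × E[Z | retained], with Z standard normal and the logistic intercept set so that the overall loss equals the stated percentage.

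| Actual loss in that arm | Bias in completer mean change | Share of the 5.9-point CID |
|---|---|---|
| 20% | 2.0 | 34% |
| 30% | 2.9 | 50% |
| 40% | 3.9 | 65% |

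The 5.9 is the value for this domain given under Measurements. The bias is proportional to the SD. An SD of 10 gives 1.3, 2.0 and 2.6 points; an SD of 20 gives 2.7, 3.9 and 5.1.

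In this scenario every posttest has been observed, so an analysis using all posttests has essentially no bias in posttest change. With equal loss by the same mechanism in every arm, the single-arm biases largely cancel in the between-arm difference. With 25% loss in one arm and 15% in another, the difference is 2.5 − 1.5, about 0.9 points before rounding.

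**The case against.** The strongest reply is that nothing in the article says incomplete cases will be deleted. An ANOVA run after imputation would satisfy both the intention-to-treat sentence and the named model, and a journal article commonly leaves missing-data handling to the full protocol or analysis plan. This stands in part: a reader might infer that the promise cannot be kept with an ANOVA at all, and that goes too far. What remains is more than an omitted detail. The article itself states the promise and the method, and the method followed as written discards measured outcomes. No stated step joins the two.

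A reader might also infer that all dropouts are excluded. The text does not support that. The sentence concerns giving up the protocol, and assessments are scheduled separately from sessions, so only a missing assessment removes someone.

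A third tempting reading is that randomisation is broken in the primary analysis and the result is materially biased. The documents do not show this. They allow 20% dropout overall, say nothing about differences between arms, and give no support for 40% in one arm. The illustration also places all loss after posttest, where using the observed posttests works best. It does not speak to loss during the 15 weeks of training, for which any method must rely on assumptions.

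**Conclusion.** The concern holds in a limited form. The named three-moment repeated-measures ANOVA, followed as written, does not deliver the promised intention-to-treat analysis for participants with a missing assessment, and it throws away scores the article says will be analysed. At the planned dropout this affects about 7 to 9 of 43 participants, provided that dropout means missed assessments.

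The cost in power is minor. Bias is the reason to act, and its size is unknown. It could be about 2 to 4 points on the primary domain under the one-arm assumptions above, and near zero if loss is similar in all arms. The conflict in the text does not depend on those assumptions; only the size of the harm does.

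**What to change.** In the Statistical analysis section, make the primary analysis a likelihood-based linear mixed model for repeated measures. It should have group, moment and group-by-moment as fixed effects, a within-person covariance across the three moments, and baseline modelled as one of the moments. State that every randomised participant with any measured score is included in the assigned arm. Treating baseline as a moment matters, because a rule requiring at least one post-baseline score would still drop those who leave before posttest. Such participants do, however, add little information on change.

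Prespecified multiple imputation before the ANOVA is an acceptable alternative. Keep the completers' ANOVA as a sensitivity analysis only, and label it as such. Say explicitly that people who stop the sessions are still invited to the posttest and follow-up already scheduled.

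The cost is a wording change and a little more analysis work, including confirming that the named software version can fit the model. No extra participants or visits are needed. The mixed model and standard multiple imputation both rely on a missing-at-random assumption, which should be stated.
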